### 2.10. Participant Timeline

Individuals who agree to participate in this study will be assessed for eligibility. Eligible patients will be randomly assigned to the intervention or the control group (Figure 1). The trial will consist of a 4-week nutritional intervention pre-surgery, with a 12-month follow-up phase. The total trial period will be 13 months. A detailed assessment schedule can be found in Table 1.

### 2.11. Sample Size and Recruitment

Sample size calculation was based on expected differences in the rate of anastomotic dehiscence of CRC surgery. According to the literature, the anastomotic leak rate in CRC patients undergoing CRC surgery varies between 3% and 50%; therefore, we estimated that for a reduction in anastomotic leak from 30% to 10%, assuming a significance level of 5% and a β power of 0.8, 48 patients in each study group would be necessary. Considering a potential 10% of follow-up losses, 54 patients per group will be recruited.

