### 2.12. Randomization and Blinding

Patients will be randomized in a 1:1 ratio after receiving a diagnosis of CRC in the endoscopic evaluation. In the control arm, patients will receive standard nutritional recommendations, while patients in the intervention arm will be advised to follow a high-fiber diet rich in PUFAs (total dietary intake of at least 30 g of fiber per day, and of at least 3 g of PUFAs per day from food, not supplements) at least 4 weeks before surgery. Simpler randomization will be computer-generated by a member of the study team at the site.

Given the nature of the intervention, neither patients nor research or medical staff will be blinded. Group assignment will be revealed to patients at the moment of participating acceptance.

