### 2.15. Statistical Methods

The analyses of this study will follow the intention-to-treat (ITT) principles. All statistical analyses will be performed with SPSS v.22.0 software (SPSS Inc., Chicago, IL, USA), considering a level of *p* < 0.05 as statistically significant. Normality of distributions will be assessed using the Shapiro–Wilk test. A descriptive analysis of the variables will be carried out with punctual estimation and a confidence interval for 95% of security, treating the continuous variables as means, standard deviation, or medians according to the distribution of the variable. Categorical variables will be presented in frequencies and percentages. Continuous variables will be compared by Student’s “t” test and by analysis of variance (ANOVA), depending on the existence of 2 or more groups in each comparison. The association between categorical variables will be analyzed using the chi-square test. Studies of correlations between the variables will be carried out using the Pearson or Spearman test based on the normality of the analyzed variables.

Per protocol analysis will be performed within participants that fulfill the intervention. This approach will be used only for the primary outcomes and will be treated as a secondary analysis. In the case of a relevant number of missing values, multiple imputation or pattern mixture models will be used.

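### 48 patients per group give about 69% power, not 80%, for leak of 30% versus 10% under the two-sided test planned; 48 fits only a one-sided calculation

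*Protocol article*

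**What the plan says.** Section 2.11 (Sample Size and Recruitment) rests the sample size on one comparison, anastomotic leak of 30% in one group and 10% in the other. The calculation and its result are given as "assuming a significance level of 5% and a β power of 0.8, 48 patients in each study group would be necessary". An allowance for losses is then added: "Considering a potential 10% of follow-up losses, 54 patients per group will be recruited". The 30% is introduced with the remark that in the literature "the anastomotic leak rate in CRC patients undergoing CRC surgery varies between 3% and 50" per cent. The section does not mention one- or two-sided testing.

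Section 2.15 (Statistical Methods) sets significance at p < 0.05 for all analyses and says: "The association between categorical variables will be analyzed using the chi-square test". Section 2.12 gives 1:1 allocation.

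**The concern.** The inputs in Section 2.11 are complete apart from sidedness, so the result can be checked. A difference of 30% versus 10% with 80% power at two-sided 5% is well known to need around 60 per group, so 48 looks too small by more than rounding or choice of formula could explain.

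This is the only sample-size justification in the article, and leak is named both in the study objective and within the primary outcome. If the calculation used a one-sided test while the analysis uses a two-sided one, the stated 80% does not belong to the analysis that will be done. Someone reading a non-significant leak comparison would then believe that the trial had a one-in-five chance of missing the planned effect, when the chance is nearer three in ten.

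**Working it through.** **Inputs.** p1 = 0.30, p2 = 0.10, 5% significance, power 0.80, 48 per group, 10% losses and 54 recruited per group (all Section 2.11); 1:1 allocation (Section 2.12); chi-square test at p < 0.05 (Section 2.15). The mean proportion is (0.30 + 0.10)/2 = 0.20.

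**Formula.** For the uncorrected chi-square test, with pooled variance under the null:

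n per group = [z_α·√(2 × 0.20 × 0.80) + z_β·√(0.30 × 0.70 + 0.10 × 0.90)]² / (0.30 − 0.10)²

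The square roots are √0.32 = 0.5657 and √0.30 = 0.5477, and z_β = 0.8416.

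**Reproducing the article's figure (one-sided 5%, z_α = 1.645).**
[1.645 × 0.5657 + 0.8416 × 0.5477]² / 0.04 = (0.9306 + 0.4610)² / 0.04 = 48.4. Power at 48 per group is 79.7%. This matches the stated 48 and 0.8.

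**The planned test (two-sided 5%, z_α = 1.960).**
[1.960 × 0.5657 + 0.8416 × 0.5477]² / 0.04 = (1.1088 + 0.4610)² / 0.04 = 61.6, so 62 per group.

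**Does another formula rescue 48?** Patients per group for 80% power, rounded up:

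| Method | One-sided 5% | Two-sided 5% |
|---|---|---|
| Unpooled variance | 47 | 59 |
| Arcsine | 47 | 60 |
| Pooled variance | 49 | 62 |
| Log odds ratio | 54 | 69 |
| Continuity-corrected | 58 | 72 |

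No two-sided method comes near 48. The closest is 59.

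**Power with the planned numbers (two-sided 5%).** With the pooled formula, power = Φ[(0.20·√n − 1.960 × 0.5657)/0.5477]. At n = 48 this is Φ[(1.3856 − 1.1088)/0.5477] = Φ(0.505) = 69.3%. At n = 54 it is Φ[(1.4697 − 1.1088)/0.5477] = Φ(0.659) = 74.5%. The exact columns sum the binomial probabilities of all tables that the test would call significant:

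| Per group | Normal approximation | Exact, Pearson chi-square | Exact, Fisher or Yates |
|---|---|---|---|
| 48 | 69.3% | 71.5% | 61.3% |
| 54 (no losses) | 74.5% | 76.3% | 67.0% |
| 62 | 80.3% | 81.0% | 74.9% |

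With 48 per group, 80% power (normal approximation) needs a fall from 30% to about 7.9% instead of 10%.

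**Losses.** 48/0.9 = 53.3, so 54; that step is right, and the error lies in the 48. From 62, the same step gives 62/0.9 = 68.9, so 69.

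**Sensitivity to the control rate (illustrative).** The article gives no effect size at other control rates. Assuming that the diet always cuts the rate to one third, as 30% to 10% does, power at 48 per group, two-sided, is:

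| Control rate | Normal approximation | Exact, Pearson chi-square |
|---|---|---|
| 20% | 48% | 52% |
| 10% | 26% | 28% |
| 5% | 15% | 11% |

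At the lowest rates events are so few that the approximation is rough.

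**The case against.** The strongest reply is that 48 is not a miscalculation. It is a correct one-sided answer (exact one-sided power at 48 is 80.6%), and the article never says two-sided. "Two-sided" is an inference from a general sentence on categorical variables that does not name leak. This is fair as to the cause, but it does not save the claim. A chi-square test on a two-by-two table has no direction, and nothing in the article announces a one-sided comparison. Either the sample size is wrong for the planned test, or Sections 2.11 and 2.15 disagree.

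Three further points have some force:

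- **Size of the shortfall.** 69% is the approximate figure. For the uncorrected chi-square test the exact power is 71.5%, and exact power first passes 80% at 59 per group, not 62. Leak is assessed within 30 days of surgery, so later losses would not affect it, and the number evaluable for leak may exceed 48. That makes 69% to 76% a fair range for the uncorrected test, all of it below 80%.
- **The control rate.** 30% lies inside the cited range, so the range does not contradict it. It simply does not single it out. The scenarios above rest on an assumed constant relative reduction. This supports showing sensitivity but is secondary to the arithmetic.
- **Scope.** The finding concerns power for leak. The primary outcome also covers microbiota change and its relationship with complications, which Section 2.11 does not size.

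A separate analysis plan, if one exists, could not cure this, because the number and the power attached to it are fixed in the article.

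**Conclusion.** The concern holds. For 30% versus 10% at two-sided 5%, 48 evaluable patients per group give 69% power (71.5% exact), against the 80% stated. Full retention of 54 per group raises this only to 75% to 76%, and Fisher's test or a Yates correction would lower it to 61% at 48. On the pooled formula the requirement is understated by 62 − 48 = 14 per group, about 23% of 62; other two-sided formulas put the requirement between 59 and 72.

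The conclusion takes the article's own rates, significance level and allocation as given, and assumes that leak will be compared with the chi-square test named in Section 2.15. It does not depend on which standard two-sided formula is used, or on whether 30% is a realistic control rate.

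**What to change.** Keep the recruitment target of 54 per group and correct Section 2.11 so that the power belongs to the test in Section 2.15. Suggested wording: *With 48 evaluable patients per group, the study has about 69% power (two-sided 5% chi-square test, normal approximation) to detect a difference in anastomotic leak of 30% versus 10%; 80% power would need 62 evaluable patients per group, or 69 allowing for 10% losses.* The exact figure of 71.5% may be quoted instead, provided the method is named.

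Also replace the phrase "β power" with power (1 − β), since β is the type II error.

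It would help to add a short table of power across control leak rates within the cited 3% to 50%, stating the effect assumed at each rate and marking the unit's own recent rate, which the article does not give.

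The cost is wording only: no change to recruitment, data collection or analysis. The price is a less favourable power statement. If the sponsor wants to keep the 80% claim, recruitment would have to rise from 54 to 69 per group, which is 30 more patients in all (2 × 15).

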### 2.12. Randomization and Blinding

Patients will be randomized in a 1:1 ratio after receiving a diagnosis of CRC in the endoscopic evaluation. In the control arm, patients will receive standard nutritional recommendations, while patients in the intervention arm will be advised to follow a high-fiber diet rich in PUFAs (total dietary intake of at least 30 g of fiber per day, and of at least 3 g of PUFAs per day from food, not supplements) at least 4 weeks before surgery. Simpler randomization will be computer-generated by a member of the study team at the site.

Given the nature of the intervention, neither patients nor research or medical staff will be blinded. Group assignment will be revealed to patients at the moment of participating acceptance.

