#### 2.13.9. Assessment of Postoperative Follow-Up and Recovery

Patients will be carefully monitored for any signs of anastomotic leak and surgical site infection symptoms (fever, leukocytosis, severe abdominal pain, etc.) within 30 days after surgery. Diagnosis of anastomotic leakage will be confirmed by radiological examination (CT scan or MRI), clinical examination, detection of serum biomarkers (CRP and procalcitonin), and post-operative endoscopy (if required). Post-operative surgical site infections will be assessed using the ASEPSIS score system. In addition, the recruited patients will be followed up for at least one year in order to evaluate recurrences of CRC, response to adjuvant therapy, and overall/disease-free survival.

Subjects will be followed up by phone every week during the intervention and for a month after surgery, and every month until the completion of the trial. Data collected from participants that withdraw from the study will be retained following the Office of Human Research Protections. No financial incentives will be provided to any of the participants.

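### Section 2.12 leaves all research and medical staff unmasked, though the diet does not require this of those who classify leaks and infections

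*Protocol article*

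**What the plan says.** Section 2.12 (Randomization and Blinding) makes a general statement on masking: "Given the nature of the intervention, neither patients nor research or medical staff will be blinded". The only reason given is the kind of intervention.

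On allocation, the same section says "Simpler randomization will be computer-generated by a member of the study team at the site" and "Group assignment will be revealed to patients at the moment of participating acceptance". Section 2.10 (Participant Timeline) says "Individuals who agree to participate in this study will be assessed for eligibility", with eligible patients then assigned. Table 1 puts consent and the eligibility screen at t−1 and allocation at t0, but its footnote places both time points at the baseline colonoscopy.

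Section 2.13.9 describes how the outcomes are ascertained. Leak is confirmed by CT or MRI, clinical examination and serum markers, with endoscopy where it is thought necessary. For infection, "Post-operative surgical site infections will be assessed using the ASEPSIS score system". No masked assessor is named for either.

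Section 2.9 makes both complications part of the primary outcome, through their relation to the microbiota change. Section 2.11 bases the sample size on leak alone: 30% against 10%, 48 patients per group, raised to 54 for 10% losses.

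**The concern.** The stated reason is narrower than the rule drawn from it. Patients on a diet know their diet, and so do the nutritionist and anyone who gives dietary advice. Someone reading a scan, scoring a wound, running an assay or fitting a model need not know the arm.

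This matters because the two clinical outcomes are not purely mechanical. Someone decides whether an equivocal collection on imaging counts as a leak, whether endoscopy is done, and how a wound is scored. If those people know the arm and expect the diet to help, borderline cases can be classed differently in the two arms. That bias favours the trial's hypothesis, and no later analysis can remove it.

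**Working it through.** **Does the reason cover the role?**

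| Role | Must know the diet? | Where judgement enters |
|---|---|---|
| Patient, nutritionist | Yes | – |
| Treating team | Hard to avoid | Clinical examination, decision to investigate |
| CT/MRI reader | No | Leak present or absent |
| ASEPSIS scorer | No | Infection score |
| Laboratory and bioinformatics | No | Little; mostly instrument-read |
| Data analyst | No | Analysis choices |

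Section 2.12 treats every row alike.

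**Inputs.** Leak rates of 30% and 10%, 48 per group, 10% losses and a 5% significance level come from section 2.11. The chi-square test comes from section 2.15.

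**The plan's own figure.** 48 / (1 − 0.10) = 53.3, rounded up to 54 per arm, 108 in total. This reproduces. I take 54 per arm as given; how the 48 was derived is a separate matter.

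**How many reclassified leaks matter.** Expected leaks are 54 × 0.30 = 16.2 and 54 × 0.10 = 5.4, so about 16 against 5. With a and c the leaks in the control and intervention arms, and b and d the patients without leak, the uncorrected statistic is

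X² = 108 × (ad − bc)² / [54 × 54 × (a + c) × (b + d)]

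- 16 v 5: ad − bc = 16×49 − 38×5 = 594; X² = 108×594² / (2916×21×87) = 7.15; p = 0.0075
- 16 v 7: ad − bc = 16×47 − 38×7 = 486; X² = 108×486² / (2916×23×85) = 4.47; p = 0.034
- 16 v 8: ad − bc = 16×46 − 38×8 = 432; X² = 108×432² / (2916×24×84) = 3.43; p = 0.064

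If the true result were 16 v 8 and three intervention-arm leaks were not called, the trial would report p = 0.0075 instead of 0.064.

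**False positives under differential classification.** Suppose the diet has no effect, the true leak rate is 30% in both arms, and assessors miss a fraction m of leaks in the intervention arm only. The observed intervention rate is then 0.30 × (1 − m). I enumerated all pairs of binomial counts at 54 per arm and applied the uncorrected two-sided 5% chi-square test. The values of m are assumptions, because the documents give none.

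| m | Observed rates | Rejection probability |
|---|---|---|
| 0 | 30% v 30% | about 5% |
| 10% | 30% v 27% | about 6% |
| 20% | 30% v 24% | about 11% |
| 30% | 30% v 21% | about 19% |

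**Order of disclosure.** Section 2.10 puts agreement before the eligibility check. Section 2.12 discloses assignment at acceptance. Taken literally together, assignment could be known before eligibility is settled. Table 1 gives the opposite order (screen, then allocation) but defines both time points by the same colonoscopy. The three places need one reading.

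**The case against.** The best defence is that full masking is impractical in a diet trial, and that the endpoints are partly objective: imaging, CRP and procalcitonin contribute to leak diagnosis, and sequencing, ELISA, multiplex and chromatography are read by instruments. This stands for the laboratory, where the risk of bias is low and coding is mainly good practice. It does not answer clinical examination, discretionary endoscopy, scan interpretation or wound scoring. Nor is this a detail that the article leaves to a fuller document: section 2.12 positively states that these staff are open.

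Three stronger readings are tempting, and the protocol does not support them.

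- **Allocation is foreseeable.** A reader might infer this from on-site generation of the list. With simple randomisation each assignment is independent, so no scheme is less predictable. Allocation would be foreseeable only if the enrolling person could see the list, which the protocol does not say. Custody of the list is a detail that an article may leave out. Section 2.4.1 also enrols consecutive patients, which limits selective entry.
- **Prognosis will be unbalanced.** Chance imbalance has expectation zero and is already reflected in the standard error. With Binomial(108, 0.5), the arms differ by 12 or more with probability 29%, but the price is small: average two-sided power for 30% v 10% is 74.1%, against 74.5% at 54/54. Blocking and stratification in an open single-centre trial are a debatable preference, and blocks would add some predictability.
- **Tumour site, or the quoted leak range, proves strong differences in patient risk.** The protocol gives no tumour-site shares. The 3% to 50% range in section 2.11 is taken from the literature and may reflect differing definitions or procedures between studies.

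**Conclusion.** The point holds for masking. Section 2.12 extends openness to people whose work the diet does not touch, and section 2.13.9 gives some of them judgement over the outcome that sets the sample size. A shift of three leaks separates a clear result from a non-significant one. One-sided under-calling of 10% to 30% would raise the false-positive rate from 5% to between 6% and 19%. These figures assume 54 analysed per arm, an uncorrected chi-square test and, for the second, a true rate of 30% in both arms. They show how sensitive the comparison is; they do not predict that staff will misclassify.

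On allocation, the conclusion is limited to two clarifications: the generator's separation from enrolment, and the order of consent, eligibility and disclosure. The change should be made before enrolment, since outcomes already assessed open are difficult to repair afterwards.

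**What to change.** 1. In section 2.12, limit the unblinded roles to patients, the nutritionist and those treating the patient.
2. State that the existing image readers, laboratory and bioinformatics staff and the data analyst work from coded identifiers without allocation.
3. In section 2.13.9, state that leak and ASEPSIS are classified against fixed written criteria, from coded records with no mention of diet. The classifier is an existing team member who takes no part in the diet and is not told the allocation.
4. State that the person who generates the list does not enrol patients, and that assignment is released only once consent and eligibility are complete. Align section 2.10, section 2.12 and Table 1 with this.

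Simple randomisation can stay, and the sample size, visits and intervention are unchanged. The cost is administrative: coding samples, scans and records, and writing the criteria. No extra assessors are needed. One limit remains: the treating team stays open, so its decisions on whom to investigate, and what it records, are not masked. The trial report should say so.

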### 2.13. Data and Sample Collection and Analysis of Variables

#### 2.13.1. Data Collection

Data and samples will be obtained at 3 different time points: at baseline, the day before CRC surgery, and one year after surgery. For data collection, a complete clinical evaluation of the patients will be performed, which will include the registration of anthropometric data (height, weight, body mass index (BMI), waist-to-hip ratio, blood pressure), information about the patient’s medication, and assessment of dietary intake using validated food frequency questionnaires (FFQs) [21]. Baseline dietary fiber and PUFA intake will be estimated from the FFQs. All participants will be asked to complete a food diary during the 4 weeks of intervention for assessment of dietary changes.

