## 1. Introduction

The gut microbiota comprises a community of about 100 trillion microbes, including bacteria, viruses, and yeasts, that have a symbiotic and mutualistic relationship with the host [1]. Although the composition of the microbiota is believed to be fairly stable in adults, it is influenced not only by host genetics, but also by environmental factors including diet, chemical exposure, and antibiotic consumption. The role of the gut microbiota in health has been extensively explored, and together with microbial-derived metabolites, they play a critical role in several physiological processes including host metabolism, immune system, and even behavior [1,2,3]. Thus, the disruption of the normal balance of gut microbiota is characterized by the depletion of commensal bacteria, overgrowth of opportunistic pathogens, and reduction in total microbiota diversity [4]. Indeed, such disturbances can lead to the development of different disorders, ranging from metabolic disturbances to cardiovascular, neurological, respiratory, and intestinal conditions, and even certain types of cancer [5].

Colorectal cancer (CRC) represents the third most common cancer worldwide and it is the second leading cause of cancer death, with an associated high economic burden [6]. The exact etiology of CRC remains unclear, although several studies have focused on the evaluation of the mechanisms involved. Most CRC cases (approximately 90%) occur sporadically (not related to the genetics of family history of the disease), and several lifestyle factors including obesity, diets with a high content of fat and (or) red and (or) processed meat, environmental pollutants, cigarette smoking, and alcohol abuse, have been associated with CRC development and progression [7]. Furthermore, there is emerging evidence that patients with CRC display significant alterations in gut microbiota, mainly characterized by an increase in opportunistic pathogens (e.g., *Enterococcaceae*, *Campylobacter*) [8] and a decrease in butyrate-producing bacteria, including *Bifidobacteria*, *Roseburia* and *Faecalibacterium prausnitzii* [9]. Overall, these alterations in the gut microbiome have been proposed to play an important role in tumor formation and progression [7,10].

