#### 2.4.2. Exclusion Criteria

Patients who fulfill any of the following criteria will be excluded from the study:Clinical diagnosis of stage IV CRC;Current gastrointestinal illness other than gastroesophageal reflux disease or hemorrhoids;Chronic liver or kidney disease;History of cardiac disease;Positive genetic test for inherited polyposis syndromes (such as familial adenomatous polyps, hereditary non-polyposis colon cancer syndromes, etc.);Alcoholism or illicit drug use;Antibiotic use within the past 2 months;Dietary supplement use including pre- or probiotics within the past month;History of intestinal cancer, inflammatory bowel disease, celiac disease, or malabsorptive bariatric surgery;Inflammatory or connective tissue disease (such as lupus, scleroderma, rheumatoid arthritis, etc.).

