#### 2.13.2. Sample Collection and Storage

Tumor biopsies will be collected during both screening colonoscopy and elective CRC surgery, and will be immediately placed in a sterile collection tube. Samples will then be taken to the Anatomic Pathology Service of the Virgen de la Arrixaca University Hospital for fixation and standard evaluations.

For stool sample collection, participants will be asked to bring their samples at baseline, the day before the surgery, and at the follow-up visit. Patients will be given an appropriate sterile collection container. If the sample is collected the day before the appointment, the patient will be asked to place the sample in the freezer until the following day. Once the sample is collected by the research staff, it will be weighed and then placed in the fridge a maximum of 4 h prior to snap-freezing in N_2_, and stored at −80 °C.

For blood sample collection, patients will be asked to fast for 12 h before the appointment. A specialized nurse will obtain two samples of 7.5 mL, one in a collection tube with clot activator for serum and one in a collection tube with EDTA for plasma isolation. Plasma and serum samples will be used for the determination of endotoxemia, intestinal permeability and inflammation markers.

The analysis of SCFAs in plasma/feces will be performed by gas chromatography-triple quadrupole mass spectrometry (GC-QqQ/MS).

All samples will be stored frozen at −80 °C at the Biobank of IMIB (registered at the Spanish Biobank Register of the Institute of Health Carlos III, ref num. PT17/0015/0038).

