## Figures and Tables

**Figure 1 jcm-11-03613-f001:**
[figure not shown]
Trial flowchart of the intervention.

**Table 1 jcm-11-03613-t001:** Assessment schedule.

	STUDY PERIOD						
	Enrolment	Allocation	Post-Allocation				Close-Out
TIMEPOINT	t_−1_	t_0_	t_1_	t_2_	t_3_	t_4_	t_5_
ENROLLMENT:							
Eligibility screen	X						
Informed consent	X						
Inclusion criteria	X						
Exclusion criteria	X						
Allocation		X					
INTERVENTIONS:							
High-fiber diet rich in PUFAs			X	X			
Standard nutritional recommendation			X	X			
ASSESSMENTS:							
Anthropometric measurements	X						
Medication	X						
Food Frequency Questionnaire (FFQs)	X						
Tumor biopsies		X		X			X
Fecal samples			X	X			X
Blood samples			X	X			X
Anastomotic leak					X		
Surgical site infections					X		
CRC recurrence						X	
Response to adjuvant therapy						X	
Disease-free survival						X	
Quality of life questionnaire						X	

t_−1_: At baseline colonoscopy; t_0_: At baseline screening colonoscopy; t_1_: Four weeks pre-surgery intervention; t_2_: Day before surgery; t_3_: 30 days post-surgery; t_4_: 1–12 months after surgery (follow-up); t_5_: 12 months after surgery.

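### The two stool samples behind the primary microbiota outcome are not timed relative to colonoscopy, bowel preparation or antibiotics, so the diet contrast may be diluted

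*Protocol article*

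**What the plan says.** Section 2.9 makes change in gut and intra-tumoral microbiota, and its relationship with anastomotic leak and surgical site infection, the primary outcome. Section 2.1 states the first aim as a comparison with the control group and adds fecal short-chain fatty acids (SCFAs).

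- **Sampling days.** Section 2.13.1: "Data and samples will be obtained at 3 different time points: at baseline, the day before CRC surgery, and one year after surgery". Section 2.13.2 repeats this for stool: "participants will be asked to bring their samples at baseline, the day before the surgery, and at the follow-up visit".
- **Order of events.** Section 2.12: "Patients will be randomized in a 1:1 ratio after receiving a diagnosis of CRC in the endoscopic evaluation". Table 1 defines its columns in the same order, from t0 onwards: "At baseline screening colonoscopy; t_1_: Four weeks pre-surgery intervention; t_2_: Day before surgery". Its row "Fecal samples" is marked at t1, t2 and t5, and not at the colonoscopy columns t−1 and t0.
- **Antibiotics.** The Introduction describes the microbiota as "influenced not only by host genetics, but also by environmental factors including diet, chemical exposure, and antibiotic consumption". Section 2.4.2 excludes patients with "Antibiotic use within the past 2 months". Section 2.8 forbids dietary supplements, including pre- and probiotics, during the intervention. It says nothing about antibiotics in that period.
- **Medication records.** Section 2.13.1 can be read as recording medication at each of the three time points. Table 1 marks it only at t−1.

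Bowel preparation and preoperative antibiotics are not mentioned anywhere in the article.

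**The concern.** The protocol regards antibiotic exposure as disturbing enough to exclude patients for two months before entry. After entry it sets no rule for a stool passed after antibiotics or cleansing, and it fixes the key stool at the day on which such exposure is most plausible.

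Three things are at stake:

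1. If preparation depletes the taxa or SCFAs that the diet raised, the difference between arms shrinks just when it is measured.
2. If the baseline stool reflects a colon still recovering from colonoscopy, recovery would look like the reversal of microbiota alterations that the study hopes to show, in both arms.
3. The analysis relating microbiota to leak and infection uses the same measurements and would inherit the same noise.

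The baseline label is a further problem. Table 1 marks the diet itself at t1, the column that holds the first stool. Read literally, the sample that the text calls baseline could be taken after the diet has begun.

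**Working it through.** **Step 1: what the article fixes about each sample**

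| Sample | Text (2.13.1, 2.13.2) | Table 1 | Relative to colonoscopy or preparation |
|---|---|---|---|
| First stool | baseline | t1, post-allocation, labelled as the four-week intervention | after colonoscopy, interval not stated |
| Second stool | day before surgery | t2, day before surgery | not stated |

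Text and table agree on the second stool. For the first they do not clearly agree on whether it precedes the diet. Section 2.13.2 lets a stool be collected the day before the appointment and kept in the home freezer. The second stool may therefore be passed one or two days before surgery, and some samples might precede any preparation while others follow it.

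**Step 2: effect of a shift common to both arms**

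Let D be the diet effect on the change in some measure, and s a preparation or recovery shift that is the same in both arms.

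- Within the diet arm: change = D + s.
- Within the control arm: change = s.
- Between arms: (D + s) − s = D.

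The randomized contrast is not biased by s. The change within the diet arm is, by the amount s.

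**Step 3: effect of losing the diet signal**

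Suppose a fraction f of the pre-surgery samples loses the whole diet effect. The expected difference is (1−f)·D + f·0 = (1−f)·D.

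- f = 30%: 70% of D remains.
- f = 60%: 40% remains.
- f = 100%: nothing remains.

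Complete loss in each exposed sample is the worst case. If exposed samples lose only half of the effect, the remainder is 1 − 0.5f, which at f = 60% is 70%. The article gives no value for f or for the loss per sample.

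**Step 4: what this could do to power (illustration only)**

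The article gives no effect size or standard deviation for any microbiota measure. Its one calculated sample size, 48 per group in Section 2.11, is for anastomotic leak at 30% versus 10%. A normal approximation gives 49 per group one-sided and 62 two-sided. That calculation does not bear on stool timing, and 48 is used here only as a number of patients.

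Take one continuous summary measure and a two-sided 5% test. The standardized difference detectable with 80% power is (1.960 + 0.842) × √(2/48) = 0.57.

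If a proportion a of the effect is lost, power = Φ(2.802 × (1−a) − 1.960):

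- a = 10%: Φ(0.562) = 71%
- a = 25%: Φ(0.141) = 56%
- a = 50%: Φ(−0.559) = 29%

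If the effect is intact but the variance rises by a ratio r, power = Φ(2.802/√(1+r) − 1.960):

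- r = 25%: 71%
- r = 50%: 63%
- r = 100%: 51%

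These figures show how sensitive the comparison would be. They do not estimate what will happen in this trial.

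**The case against.** The strongest reply is that the premise is not in the article. Neither cleansing nor preoperative antibiotics is mentioned, and the influences that the Introduction names do not include cleansing. Collection instructions may also sit in the full protocol or in the patient information sheet, neither of which is shown. This stands: exposure is an assumption and its extent is unknown. The reply does not remove the point, because the sampling day is something the article states, and following it could degrade the primary measurement.

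A reader might infer that both samples are taken in a disturbed bowel and that the randomized comparison is therefore confounded. The documents do not support this. Table 1 does not place the baseline stool at colonoscopy. Both arms are randomized after endoscopy and sampled on one schedule, and Step 2 shows that a common shift cancels. Bias between arms would need exposure or intervals to differ by arm, and nothing in the article shows that they do.

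There is also partial handling. Home collection may put some pre-surgery stools ahead of any preparation. Section 2.13.1 may intend medication to be recorded at each time point, and Section 2.13.9 provides weekly telephone contact during the intervention. None of these sets a rule for samples passed after exposure.

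Finally, part of the outcome cannot be helped by moving the stool sample: "Tumor biopsies will be collected during both screening colonoscopy and elective CRC surgery". The timing of the tissue samples follows the procedures themselves. That limits the remedy but is no reason to leave the stool timing open.

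**Conclusion.** The concern holds as a problem of sample timing with a conditional cost. The article fixes the only post-diet, pre-surgery stool at the eve of bowel surgery. It leaves the baseline stool at an unstated interval after colonoscopy, in a column that reads as post-allocation and on diet. It controls antibiotics only at entry, and Table 1 conflicts with one reading of the text on whether medication is recorded later.

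If some patients are exposed to cleansing or antibiotics before the second stool, the between-arm difference in 16S composition and fecal SCFAs may be attenuated or noisier, and so may the link with leak and infection. That link is not a randomized contrast, so the cancellation in Step 2 does not protect it. The size cannot be derived from the article. The factor (1−f) is an upper limit on the dilution for a given f.

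Within-arm change should not be read as a diet effect. The randomized contrast remains valid as a comparison, and it would be an overstatement to call it biased.

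**What to change.** In Sections 2.13.1 and 2.13.2 and in Table 1:

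1. Define the pre-surgery stool as the last one passed at home on the study diet before any bowel preparation or preoperative antibiotic begins.
2. Reconcile Table 1 with the text so that the baseline stool is collected before the diet starts. Record its interval from colonoscopy. Waiting for this sample must not delay allocation or surgery.
3. Record the dates of any cleansing and any antibiotic between the two samples, and align the medication row of Table 1 with Section 2.13.1.
4. Add a sensitivity analysis that excludes exposed samples.

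Home collection and freezing are already allowed, so the change is mainly to patient instructions and schedule wording. The costs are slightly longer home freezing, which should be the same in both arms because it is a handling variable in its own right, and one extra case-report field. Clinical preparation is unchanged. The tumor biopsies stay where they are, and the recorded exposure dates will at least help in interpreting them.
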